### Innovative Recruitment

Participants are recruited using both passive and active strategies. In the *passive strategy*, the study team distributes flyers at the Johns Hopkins outpatient oncology clinics, patient education rooms, survivorship clinics, and survivorship meetings to spread study awareness among clinic staff, particularly nurse educators and managers. With the *active strategy* for recruitment, the Epic reporting function is used to generate patient lists of those who match the screening criteria at selected Johns Hopkins clinics in Maryland. Screening for existing cancer patients takes place at the outpatient clinics, by specific providers and on follow-up weekly appointments only; potential participants must have a prior diagnosis of a cancer of interest, a BMI of 25 or above, and reside in the state of Maryland. Once a list is generated, the study team actively reaches out to each patient after the outpatient clinic visit to provide them with study information. All candidates identified by either strategy are included in an electronic Clinical Research Management System (CRMS) linked to the EMR. The study coordinator updates the candidate’s status regularly based on candidate eligibility, consent, and enrollment type. Reasons for ineligibility are also recorded in CRMS. Data on the number of eligible patients, along with reasons for not enrolling can be captured and reported to the institution’s Institutional Review Board (IRB). Weekly automated reports can be generated from CRMS to track enrollment and pending statuses.

Once eligibility is determined, an IRB-approved consent designee obtains an IRB-approved written informed consent form (ICF) in the outpatient clinic or at the study office. A signed and dated IRB-approved ICF is documented in a secure participant study file prior to initiating study-related procedures. As part of the consent process, the study team 1) informs each participant of study procedures and requirements and allows sufficient time for the individual to decide whether to participate in the study; 2) answers questions about the details of the study; and 3) ensures that the ICF is approved by the IRB when an amendment to the study protocol is made. Participants are free to withdraw consent for participation in the study at any time, without affecting their current or future treatment.

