### Randomization

Participants are randomized with an allocation ratio of 1:1:1 to the control self-driven arm (Group A), *Coachtext* (Group B), or *MyCoach* (Group C). Once a participant signs the IRB approved ICF, the randomization procedure is conducted. Since the study is recruiting cancer survivors, the team collects data regarding certain prognostic factors that may affect physical performance and thus ability to perform physical activity, including 1) types of cancer; 2) age; and 3) BMI. To attenuate the impact of such factors the study team is using Stratified Permuted Block Randomization, which generates strata by sex, age group, and BMI, then assigns a unique number for each block. At randomization, the PI or study coordinator assign strata by participant variables, then assign the arm after generating a random number out of all possible blocks using random.org. Subsequent assignment is linked to the strata in which the new participant belongs. If the prior block under the selected strata is completed or not started, a new block is selected/opened using random.org. Only the principal investigator (PI) and the study coordinator are designated to conduct the randomization procedure. The PI or the study coordinator report the randomization procedure to the participant orally and record it on the randomization sheet. The study data analyst is blinded to the random assignments.

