### Statistical Analyses

As the primary outcome variable is the 4-week change from the baseline in the average number of steps per day, the primary analysis will use a two-sample t-test to compare each active intervention arm with the control arm based on intent-to-treat strategy. A Bonferroni correction will be used to adjust for multiple comparisons.

For the secondary outcomes (activities bouts, fragmentation, and patterns), a linear regression model will be fitted for the 4-week change from the baseline in the number of steps and duration of activity bouts each day. The independent variables include the baseline number of steps, study arm (modeled by two dummy variables for the two active treatment arms, and the control arm is treated as reference group), and any potential baseline confounding factors. Poisson regression will be used to analyze the total number of activity bouts, fragmentation indices, and variability indices. The independent variables include baseline number of steps, study arm, and any potential baseline confounding factors as the independent variables. In all analyses, data will be properly transformed to fit the model assumption before regression analysis. Although missing data is not anticipated to be a challenge, small amount of non-wear time for charging, bathing, etc. will have minimal effects on the primary study aim since it depends on the average steps across the intervention period. Since Stratified Permuted Block Randomization is being employed, we will consider minimization to balance interventions simultaneously over several prognostic factors to ensure equal distribution across arms. To date nearly 80% of the target population has been enrolled, and only one participant stopped wearing the tracker one day a week for religious reasons.

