## Discussion

### Study Rationale

This study designed, developed, and launched a clinical trial to investigate the effect of novel emerging technologies to assist cancer survivors to become more active in their daily lives. The study uses innovative technology and methods to apply autonomous artificial intelligent agents as an intervention. This is an affordable, scalable, and easily deployed personalized and tailored intervention that has the potential to transition from the research setting to general use. It is important to offer a scalable and affordable solution that can assist cancer survivors to become more active. Given the wide general utility of the technology and applicability of the outcome of interest, this approach may also be applicable to the general population with slight modification of the intervention and testing in a larger population study.

The trial operation is minimalist in design and effort. Recruitment activities and enrollment were designed and developed with a focus on low cost and efficiency. The study team developed innovative prescreening in the EMR environment, with remote intervention deployment and data collection processes. The entire trial is operated by the PI and the study coordinator. Data collection processing is autonomous and no interference from the study team or participants is needed. The data flow on a minute-by-minute basis to a structured database for real time analysis allows decision support for the artificial intelligent agent. The same data will be used subsequently to assess the effect of the intervention on the primary outcome. The trial’s recruitment is currently active and eligible consented patients have been enrolled.

Intelligent Agents (IA) are not new. Stuart Russell and Peter Norvig researched this topic extensively in their leading textbook in Artificial Intelligence—Artificial Intelligence: A Modern Approach [18]. Russell and Norvig state that the core behavior of an agent is goal-directed and therefore they refer to agents as “Rational Agents”. These agents can be classified into five classes: simple reflex agents, model-based reflex agents, goal-based agents, utility-based agents, and learning agents [18]. Amazon Alexa and our agent (*MyCoach*) use a combination of different agent classes. The study team chose to use different classes to adapt to the user’s intents.

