Artificial intelligence (AI) has promising wide applications in translational research. Enablers to use such technologies, including tools and developer kits, are widely available for interested researchers, while codes libraries are shared among most researchers and powerful platforms are widely used in the form of mobile devices and home speakers. The current study provides insight beyond the target outcomes by its efficient operation. The entire study is operated by 1-2 persons. This is possible because most of the study components, including data collection, have been automated or enhanced by technology solutions. Even the start of the intervention is automated. The study team also automated the instructional communication via scheduled automated emails based on each participant enrollment date. The written consent process is still in paper format, a requirement of the University IRB.

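### No described step hides the rest of an open permuted block from the two people who run the trial, and a sentence on minimization conflicts with the stated allocation method

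*Protocol article*

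**What the plan says.** All references are to the protocol article.

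- **Who randomizes (Randomization):** "Only the principal investigator (PI) and the study coordinator are designated to conduct the randomization procedure".
- **How (Randomization):** strata are formed by sex, age group and BMI, and each block carries its own number. The operator places the participant in a stratum, "then assign the arm after generating a random number out of all possible blocks using random.org". Later participants in that stratum follow the open block. "If the prior block under the selected strata is completed or not started, a new block is selected/opened using random.org".
- **Timing and record (Randomization):** the draw takes place after the consent form is signed. The result is told to the participant and entered on a randomization sheet.
- **Who runs the trial (Study Rationale):** "The entire trial is operated by the PI and the study coordinator"; and again, "The entire study is operated by 1-2 persons".
- **Screening (Innovative Recruitment):** "The study coordinator updates the candidate’s status regularly based on candidate eligibility, consent, and enrollment type". Consent is taken by a designee approved by the review board.
- **Masking (Randomization; Blinding):** the data analyst is blinded and participants are not. No masking of the allocation sequence is described.
- **Second allocation method (Statistical Analyses):** after noting that stratified permuted blocks are in use, the text says "we will consider minimization to balance interventions simultaneously over several prognostic factors to ensure equal distribution across arms".

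**The concern.** A permuted block is a complete short sequence. Whoever draws its number and looks up the arm for the first participant is in a position to see the arms for everyone else in that block. Here that person also runs recruitment.

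The stratum can largely be worked out before contact. BMI is one of the criteria used to pull candidate lists from the medical record, and sex and age are not hidden at that stage. An operator who knows the next arm in a stratum could, even without intent, influence which candidates are pursued, how the judgment-based eligibility criteria are applied, and when someone is brought to consent. Of 75 screened, 39 were enrolled, so there is room for selection. Replacements for run-in dropouts pass through the same hands, and allocation comes before the run-in.

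Selection at entry changes the composition of the arms. Sensor-measured steps and a blinded analyst cannot undo that, and with 14 per arm a few selectively placed participants matter.

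The minimization sentence raises a separate problem. Minimization is a different allocation method from stratified permuted blocks, so the article does not leave one settled method for the analysis to reflect.

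**Working it through.** **Inputs from the article.** Target N = 42, allocation 1:1:1, strata by sex, age group and BMI. Enrollment is given as 39 in the abstract and in Trial Status, and as close to 80% of target in Statistical Analyses.

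**Assumptions, because the article gives no value.** Block size B = 3, 6 or 9 (multiples of 3 for 1:1:1). Number of strata 8 (2 × 2 × 2), 12 or 18. The rest of an open block is visible to the operator.

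**Step 1: full blocks.** Only the first assignment in a block is unknown beforehand, so the known share is (B − 1)/B: 2/3 = 67%, 5/6 = 83%, 8/9 = 89% for B = 3, 6, 9.

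**Step 2: incomplete blocks.** A stratum with c participants opens ⌈c/B⌉ blocks, so

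known share = 1 − (blocks opened)/N.

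Hand check with 8 nearly equal strata (six of 5 and two of 6, total 42): B = 3 opens 16 blocks, giving 1 − 16/42 = 62%; B = 6 opens 8 blocks, giving 1 − 8/42 = 81%. Random variation in stratum sizes lowers these somewhat. Means over 3,000 simulated splits of 42 participants across equally likely strata:

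| Strata | B = 3 | B = 6 | B = 9 |
|---|---|---|---|
| 8 | 60% | 76% | 80% |
| 12 | 57% | 71% | 72% |
| 18 | 52% | 61% | 61% |

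With N = 39 the range is 51% to 79%. Unequal stratum probabilities at N = 42 give 54% to 80%. The weakest case at N = 42 (18 equal strata, B = 3) has a 5th to 95th percentile range of 48% to 57%, so more than half is true there on average but not in every realization.

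**Step 3: what a hidden sequence would leave.** Participants are unblinded, so with fixed blocks a recruiter who tracks past arms can still deduce some assignments with certainty.

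- B = 3: the last of three is always determined, 1/3.
- B = 6: the sixth is always determined, and the fifth only if the last two arms are equal (probability 1/5). That gives (1 + 1/5)/6 = 1/5.

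The fair comparison in full blocks is therefore 67% against 33% for B = 3, and 83% against 20% for B = 6. The one-in-three chance of a correct blind guess is a different measure and should not be set beside the share known with certainty, even though it equals the B = 3 figure numerically.

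**Step 4: assignments still open.** 39/42 = 92.9%, which leaves 3. For the other statement, 33/42 = 78.6% leaves 9 (80% of 42 is 33.6). The two enrollment figures may have different dates.

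**The case against.** **Visibility is inferred.** The article does not say who holds the key from block number to sequence, and a condensed article may omit such mechanics. This stands as a limit on certainty: the percentages are conditional. It does not remove the point, because the article does describe the procedure, and in it the same two people draw the number and assign the arm.

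**Consent comes first.** Eligibility and consent precede the draw, and a designee takes consent. This is a real safeguard against changing one's mind after seeing the arm. It does not cover foreknowledge from a block already open, and the designee is not described as independent of the two operators.

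**Stronger readings that the article does not support.**

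- *Assignments were in fact foreseen or steered.* Nothing in the article shows this.
- *A change to minimization is planned at about 80% enrollment.* The text says only that it will be considered. The enrollment figure sits in another sentence, about recruitment progress and one participant's tracker wear, and is not given as a starting point for a new method. The Randomization section describes stratified blocks in the present tense.
- *There is no audit trail.* A randomization sheet exists. What is not described is a sequence fixed in advance to check it against.

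**Little is left to protect.** This is correct. Most of the value of the correction now lies in honest reporting.

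**Conclusion.** The point holds as a weakness in allocation concealment as described. The people who can influence entry also draw the block and read the arm, and no step hides the remainder from them. If open blocks are visible, about 52% to 80% of the 42 assignments would be known beforehand. This rests on assumed values of 8 to 18 strata and blocks of 3 to 9. Concealment with fixed blocks would still leave about 1/3 (blocks of 3) or 1/5 (blocks of 6) deducible in full blocks, so the avoidable part is large but is not the whole figure.

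The minimization sentence is a smaller, separate defect. It is inconsistent with the stated method and should be removed, but it does not show that a mixed scheme will be used. The whole point merits correction and disclosure; it does not by itself invalidate the pilot.

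**What to change.** 1. **Conceal what remains.** For all remaining and replacement assignments, complete the open blocks and generate later ones by script with varying block sizes. Hold the sequence on the existing study server under access that neither the PI nor the coordinator has; storing it where they can read it would leave the problem in place. Release one arm at a time, only after eligibility and consent are locked.
2. **Settle the method.** Delete the minimization sentence.
3. **Handle residual imbalance in the analysis.** Replace the unadjusted t-test for the primary comparison with a model that adjusts for sex, age group, BMI and baseline steps. The article already plans baseline steps as a covariate in its secondary regression models.
4. **Report.** State that no concealment from the operators was described for earlier assignments, and use the randomization sheet to document them.

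**Cost.** A short script, an access restriction and a small change to the primary model, to be made before the analyst is unblinded. It protects only about 3 assignments by the 39-of-42 count, or up to about 9 by the lower enrollment statement, plus replacements. It cannot repair assignments already made.

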### Intervention

Those assigned to the control arm (A) receive educational materials and are advised to increase physical activities to 10,000 steps per day. Participants in the control arm receive National Cancer Institute (NCI) printed educational materials providing summary evidence about the benefits of exercise for cancer survivors [14]. While the publication by NCI is meant to encourage participants to become active, it does not provide specific goals or a structured program. As in the other arms, participants in the control arm are expected to use walking as a recommended activity type. Participants in this arm receive the same activity tracker (Fitbit Charge 2 HR) and its companion mobile application as those in the other two study arms.

Participants in the *Coachtext* arm (B) receive remote coaching using personalized automated data driven text messages, a system designed and developed by the study team that provides text messages to the participant’s cellphone. Those enrolled in this arm provide their cellphone number and complete an online questionnaire about their daily routine, pet ownership, and household information to establish their text messages preferences. The text messages are delivered, based on participant preferences, three times per day for four weeks after the seven-day run-in (baseline data collection). Each message is composed and pushed based on each participant’s real time physical activity performance, taking into account the prerecorded preferences and household information. A sophisticated algorithm reads the participant’s data in the server, then mixes it with the hourly step performance captured by the wearable sensor transmitted to the server, and generates a personalized coaching message. The *Coachtext* algorithm has a flexible goal-based design using data to support its choice on how and when to push a message. The *Coachtext* incoming and outgoing data as well as the algorithm are housed in a server approved by the Institutional Review Board. Figure 2 illustrates the *Coachtext* design.

*Coachtext* is completely automated; however, the study investigators can intervene if needed. This is a precautionary measure that was included in case of system failure or errors, and/or to update the knowledge library of *Coachtext* database. However, no such events have been recorded so far, and no knowledge was changed or newly generated. The study team designed and developed the message content after extensive literature reviews and expert opinions. The messages are formulated based on health behavioral theories with a focus on feedback about actual performance vs expected and habit formation to reach expected performance [15]. Health belief theory is also integrated by offering contents to build knowledge about the benefits of exercise for cancer patients [16]. In addition, the study investigators can check a daily dashboard plotting each participant’s physical activities. The study PI also receive notification in case the system failed to generate or deliver any message on time. As of November 2017, no such event has been recorded. An example of the generated messages includes:

preferred name>, you were too inactive yesterday. You got <#step_count_yesterday steps>. Your goal is 10,000. How about taking a stroll today with <dog_name>. Aim for 10 minutes or more. This will not only be good for you, but is essential to <dog_name's>good health

**Figure 2 figure2:**
[figure not shown]
*Coachtext* architecture. JHU: Johns Hopkins University.

The third arm is *MyCoach* (C), a conversational Artificial Intelligent Agent delivered via the Amazon Echo home speaker. The investigator chose the Amazon Alexa platform because it has a developer kit that can be utilized to build one’s own voice skill. The study team designed and developed *MyCoach* with knowledge representation, planning, learning, perception, and natural language processing (NLP) using the Alexa developer kit. *MyCoach* uses a sophisticated learning algorithm to enable its functions, and its algorithm uses data from different sources, including, but not limited to the: patient study file, physical activity wearable sensor, Echo home spatial microphones, knowledge library, Amazon music library, intents & responses library, user’s calendar, geo/location data, National Weather Service UV index, and more. *MyCoach* is delivered to the participant through an Amazon Echo speaker [17]. Amazon Alexa was used as an NLP engine to receive the participant’s requests/questions (known as the *Intent*) and the Alexa voice to deliver the answer/advice/coaching (*Response*). In addition, the Alexa companion cellphone application is used to deliver visual responses if needed. The study team designed the *MyCoach* user experience to mimic health coaches. Therefore, the user-initiated request/Intent is the core functionality of *MyCoach*, and no advice/health tip/comments is delivered by *MyCoach* unless the participant requests *MyCoach* advice.

The *Intent* has two triggers words (*Invocations*). The first *Invocation* to ignite/turn on Alexa Echo device is “Alexa,” the second, “My coach,” is to alert Alexa that this intent needs to be routed to the *MyCoach* server, within the Johns Hopkins University firewall, to process and generate outputs. For example, the user will say “Alexa, ask My Coach...”, etc. The Alexa NLP engine is used to process the user’s spoken intent into structured representation. The structured request is routed to the *MyCoach* server for processing. During processing, a complex algorithm utilizes multiple data sources and real-time wearable sensor readings to generate a *Response*, which could be a text and/or a graphical response. The servers push the text Response(s) to Alexa, and the graphical responses to the companion app on the user’s cellphone. Alexa converts the text to speech and voices it through the Echo speaker at the user’s home (see Figure 3).

*MyCoach* performs a variety of functions. For example, it offers feedback, assists in formulating habits, provides reminders and alarm, informs the user if he/she need UV skin protection before heading outside, provides health tips and knowledge, and more. Like the participants in *Coachtext*, participants in the *MyCoach* arm also experience a question session to personalize coaching, but in voice conversation format with Alexa/ *MyCoach*
**.** All functions are operated by voice, and since hundreds of ways to state the same intent were programmed by the study team to accommodate each different user’s style, no prior training is needed to request each function. An example of intents is as follows:

Alexa, I’m planning to go out for a walk. Ask my coach if I need sunscreen.User

Alexa, ask my coach, “How is my progress so far?”User

Alexa, I’m not making good progress; ask my coach for health tips to help me become more active.User

The study utilized Amazon’s prebuilt user-machine interaction data to track participant utilization of *MyCoach*. Screen shots of the data visualization dashboard used to track interaction by type, time, and intent are provided in Multimedia Appendix 1.

